## Abstract

**Background:**

Coronary microvascular disease (CMVD), particularly ischemia with non-obstructive coronary arteries (INOCA)-related CMVD, is associated with recurrent angina, impaired quality of life, and an increased risk of adverse cardiovascular outcomes. Although recognition of this condition is increasing, treatment options remain limited, and many patients continue to have symptoms despite conventional medical therapy. Acupuncture has shown potential as an adjunctive therapy for angina-related symptoms and other cardiovascular conditions. However, high-quality evidence for INOCA-related CMVD remains scarce. This trial aims to evaluate the efficacy and safety of acupuncture as an adjunct to conventional medical therapy in patients with INOCA-related CMVD.

**Methods:**

This prospective, single-center, randomized, sham-controlled, parallel-group pilot trial will recruit 60 participants with INOCA-related CMVD at Guang'anmen Hospital, China Academy of Chinese Medical Sciences, Beijing, China. Eligible participants will be randomly assigned in a 1:1 ratio to an acupuncture group or a sham acupuncture group. Both groups will continue guideline-directed conventional medical therapy. The acupuncture group will receive true acupuncture at Dabao (SP21), Neiguan (PC6), Danzhong (CV17), Xinshu (BL15), and Geshu (BL17), while the sham group will receive non-penetrating sham acupuncture at the same acupoints with the same schedule. Treatment will be given three times weekly for 4 consecutive weeks, followed by a 4-week follow-up. The primary outcome is the response rate at week 4, defined as the proportion of participants with an increase of at least 5 points in the Seattle Angina Questionnaire summary score from baseline. Secondary outcomes include changes in SAQ scores, angina attack frequency, EuroQol 5-Dimension 5-Level questionnaire, traditional Chinese medicine syndrome score, nitric oxide, endothelin-1, and high-sensitivity C-reactive protein. Additional assessments include Clinical Global Impression–Improvement, expectancy and credibility assessments, and blinding assessment. Safety evaluation includes monitoring adverse events and serious adverse events throughout the trial.

**Discussion:**

This pilot trial will provide preliminary evidence on the safety and potential efficacy of acupuncture for INOCA-related CMVD and may help clarify its effects on angina-related health status, quality of life, and selected endothelial and inflammation-related markers. The findings are expected to inform future larger multicenter confirmatory trials.

**Clinical Trial Registration:**

International Traditional Medicine Clinical Trial Registry (http://itmctr.ccebtcm.org.cn/), Identifier ITMCTR2026000515.

## Introduction

1

Coronary microvascular disease (CMVD) is a clinical syndrome caused by structural and/or functional abnormalities of the coronary microcirculation in the absence of obstructive epicardial coronary artery disease (1, 2). Its major pathophysiological mechanisms include endothelial dysfunction, impaired vasomotor regulation, and reduced microvascular perfusion. In recent years, CMVD has been increasingly recognized as an important phenotype within chronic coronary syndromes and a major mechanism underlying persistent angina in patients with angina and non-obstructive coronary arteries (ANOCA/INOCA) (3, 4).

CMVD is common in patients with ANOCA/INOCA, particularly in women, although its prevalence varies according to diagnostic modality and threshold definitions (5, 6). More importantly, CMVD is not a benign condition. Patients with coronary microvascular dysfunction often experience recurrent chest pain, impaired functional capacity, and reduced quality of life, and may also face an increased long-term risk of adverse cardiovascular outcomes (7, 8). Despite growing awareness of this condition, its clinical management remains challenging. Although recent guidelines have emphasized early recognition and mechanism-based treatment, access to specialized diagnostic testing is still limited, and many patients continue to have persistent symptoms despite standard anti-anginal therapy and risk-factor control (2, 9, 10).

Acupuncture has shown potential as a non-pharmacological adjunctive therapy for cardiovascular diseases, particularly chronic stable angina. Randomized trials and evidence syntheses suggest that acupuncture may help relieve angina symptoms and improve patient-reported outcomes (11–14). Emerging reviews on CMVD and traditional Chinese medicine further suggest that acupuncture may exert beneficial effects through modulation of autonomic function, endothelial function, inflammation, and microcirculatory regulation (15–17). However, the current evidence for acupuncture specifically in CMVD remains limited. Most published studies are small, single-center, and methodologically heterogeneous, and important shortcomings remain in diagnostic standardization and outcome assessment (15, 18–20).

Therefore, a rigorously designed randomized controlled trial is needed to evaluate the efficacy and safety of acupuncture for INOCA-related CMVD. In the context of contemporary ANOCA/INOCA frameworks, the target population of this trial is symptomatic INOCA-related CMVD, corresponding mainly to coronary microvascular dysfunction characterized by adenosine-mediated impaired vasodilation and/or abnormal vasoconstriction of the coronary microvasculature, rather than epicardial vasospastic angina or asymptomatic coronary microvascular dysfunction. The present study is designed as a prospective, single-center, randomized, sham-controlled exploratory trial to assess whether acupuncture, in addition to conventional therapy, can improve angina-related health status, quality of life, and endothelial and inflammatory markers in this population. By incorporating validated patient-reported outcomes, such as the Seattle Angina Questionnaire, together with biomarker-based evaluation, this trial is expected to provide more standardized preliminary evidence for acupuncture in INOCA-related CMVD and to inform the design of future larger multicenter studies (21).

## Methods and analysis

2

### Study design

2.1

This is a prospective, single-center, parallel-group, randomized, sham-controlled exploratory trial. The protocol was prepared in accordance with the SPIRIT 2025 statement (22), with the corresponding checklist provided in Supplementary Table S1, and the acupuncture intervention is reported with reference to the revised STRICTA recommendations (23), as detailed in Supplementary Table S2. Sixty eligible participants will be randomly assigned in a 1:1 ratio to the acupuncture group or the sham acupuncture group.

Each participant will be followed for 8 weeks, including baseline assessment within 24 h after enrollment, 4 weeks of treatment, and 4 weeks of post-treatment follow-up. The primary objective is to evaluate the efficacy and safety of acupuncture as an adjunct to conventional therapy for INOCA-related CMVD and to explore its potential effects on angina-related health status, quality of life, endothelial function, and inflammation-related biomarkers.

This study protocol is version 1.0. It has been approved by the Ethics Committee of Guang'anmen Hospital, China Academy of Chinese Medical Sciences, and was registered with the International Traditional Medicine Clinical Trial Registry on March 13, 2026 (registration number: ITMCTR2026000515). The trial will be conducted in accordance with the Declaration of Helsinki. Eligible participants will be enrolled voluntarily and will provide written informed consent before any study-specific procedure. The study flowchart and the schedule of enrollment, interventions, and assessments are shown in Figure 1 and Table 1.

**Figure 1 F1:**
[figure not shown]
The study flowchart. SAQ, Seattle Angina Questionnaire; EQ-5D-5L, EuroQol 5-Dimension 5-Level questionnaire; TCM, traditional Chinese medicine; ET-1, endothelin-1; NO, nitric oxide; hs-CRP, high-sensitivity C-reactive protein; CGI-I, Clinical Global Impression-Improvement.

**Table 1 T1:** Study schedule.

Stage	Trial period			
	Enrollment	Allocation	Treatment	Follow-up
Timepoint	−1d	0d	4w	8w
Enrollment				
Eligibility screening	×			
Informed consent	×			
Baseline assessment		×		
Randomization		×		
Interventions				
Acupuncture plus conventional therapy		←--------------→		
Sham acupuncture plus conventional therapy		←--------------→		
Assessments				
Demographic and baseline clinical characteristics		×		
Overall clinical response rate			×	
SAQ		×	×	×
Angina attack frequency		×	×	×
EQ-5D-5L		×	×	×
TCM syndrome score		×	×	×
Laboratory tests (NO, ET-1, hs-CRP)		×	×	
Patients’ expectation for acupuncture		×		
Credibility assessment		×	×	
CGI-I			×	×
Blinding assessment			×	
Safety assessment and adverse events		×	×	×

d, day; w, week; SAQ, Seattle Angina Questionnaire; EQ-5D-5L, EuroQol 5-Dimension 5-Level questionnaire; TCM, Traditional Chinese Medicine; NO, nitric oxide; ET-1, endothelin-1; hs-CRP, high-sensitivity C-reactive protein; CGI-I, Clinical Global Impression–Improvement.

### Participant screening

2.2

#### Diagnostic criteria

2.2.1

##### Diagnostic criteria for INOCA-related CMVD

2.2.1.1

According to the Chinese expert consensus on the diagnosis and treatment of coronary microvascular diseases (2023 edition) (1), INOCA-related CMVD will be diagnosed when all of the following conditions are satisfied:
Typical clinical symptoms are present.At least one objective indicator of myocardial ischemia is documented, including typical exertional or spontaneous chest pain accompanied by ST-segment depression on electrocardiography; reversible myocardial perfusion defects on stress single-photon emission computed tomography (SPECT); reduced coronary flow reserve (CFR <2.0) assessed by Doppler echocardiography; reduced myocardial perfusion reserve index (MPRI <2.0) on cardiac magnetic resonance imaging (CMR); or metabolic evidence of myocardial ischemia on positron emission tomography (PET).Coronary angiography shows normal coronary arteries, irregular vessel walls, or luminal stenosis of <50%.In patients with a high clinical suspicion of CMVD despite CFR ≥ 2.0, an intracoronary acetylcholine provocation test may be performed under close monitoring when clinically indicated. The presence of epicardial coronary spasm during acetylcholine testing will lead to exclusion. In contrast, reproduction of angina symptoms and ischemic ST-T changes in the absence of epicardial coronary spasm will be considered compatible with microvascular vasomotor dysfunction.Non-cardiac chest pain and other cardiac diseases are excluded, including vasospastic angina, cardiomyopathy, myocarditis, and valvular heart disease.

##### Traditional Chinese medicine syndrome differentiation criteria

2.2.1.2

The diagnostic criteria for qi deficiency and blood stasis syndrome will be based on the Guidelines for the Diagnosis and Treatment of Coronary Microvascular Disease in Traditional Chinese Medicine (24).
Primary symptom: chest pain or chest tightness, usually triggered or aggravated by exertion.Secondary symptoms: ① shortness of breath and fatigue;② lassitude and reluctance to speak;③ palpitations and spontaneous sweating;④ pale or dusky complexion.Tongue manifestation: enlarged, pale-dark tongue.Pulse manifestation: deep and choppy pulse.A diagnosis will be made when at least one primary symptom is present, together with two or more secondary symptoms, in combination with the corresponding tongue and pulse manifestations.

#### Inclusion criteria

2.2.2

Participants will be eligible for inclusion if they meet all of the following criteria:
Aged 18 to 80 years, regardless of sex;Meeting the Western medicine diagnostic criteria for INOCA-related CMVD;Meeting the traditional Chinese medicine diagnostic criteria for qi deficiency and blood stasis syndrome;Having a relatively stable medication regimen during the month before enrollment and being able to complete acupuncture treatment and follow-up;Willing to accept random allocation, able to understand the study procedures, and providing written informed consent.

#### Exclusion criteria

2.2.3

Participants will be excluded if they meet any of the following criteria:
Acute coronary syndrome or coronary revascularization within the previous 3 months; significant valvular heart disease, cardiomyopathy, or heart failure of New York Heart Association class III-IV;Definite or clinically suspected epicardial vasospastic angina, based on clinical history, electrocardiographic findings during symptoms, angiographic evidence, or acetylcholine provocation testing when available;Severe hepatic or renal dysfunction, active bleeding, or coagulation disorders;Pregnancy or lactation;Contraindications to acupuncture, such as local infection, severe skin disease, or implanted devices located in areas at risk during needling;Allergy or contraindication to background medical therapy.

### Recruitment process

2.3

All recruiters and study personnel will receive standardized training before trial initiation. Recruitment advertisements will be posted in outpatient clinics and wards of Guang'anmen Hospital, and recruitment information will also be disseminated through the hospital's official WeChat public platform.

### Written informed consent

2.4

Before study initiation, recruiters will provide potential participants with a detailed explanation of the possible benefits, risks, and discomforts associated with participation. After reviewing the paper informed-consent form, participants who agree to enroll will sign the form in duplicate, with one copy retained by the investigator and the other by the participant or the participant's legal representative. Contact information will be collected to facilitate communication during treatment and follow-up. Participants who decline participation, or who withdraw at any time, will not be affected with respect to routine medical care or any other rights and interests.

### Participant adherence

2.5

To improve adherence, participants will receive education on the epidemiology, diagnosis, and treatment of CMVD, together with a clear explanation of the study background and the potential benefits and risks of acupuncture. Investigators will maintain close contact with participants and, when appropriate, family members, and will provide reminders for treatment sessions and follow-up visits. All protocol-required laboratory tests, examinations, and questionnaire assessments will be provided free of charge. For participants who discontinue the study, treatment status and reasons for withdrawal will be documented to support adherence assessment.

### Randomization, allocation concealment, and blinding

2.6

An independent statistician will generate a simple 1:1 randomization sequence without stratification using SAS 9.4 and a prespecified random seed. Considering the exploratory nature and relatively small sample size of this pilot trial, stratification by sex, age, or baseline SAQ score will not be performed. Allocation will be concealed in sequentially numbered, sealed, opaque envelopes prepared and kept by staff members not involved in recruitment, treatment, or outcome assessment. Each envelope will be opened in numerical order only after eligibility has been confirmed and baseline assessment has been completed. Participants, outcome assessors, and statisticians will remain blinded to group assignment. Outcome assessors will not participate in treatment delivery or allocation procedures. The dataset provided to the statistician will use coded group labels, and the allocation list will not be released until the primary analysis has been completed. Acupuncturists cannot be blinded because of the nature of the intervention. Emergency unblinding will be allowed only when knowledge of the allocated intervention is essential for clinical management of a serious adverse event or another urgent medical situation. Any emergency unblinding will be authorized by the principal investigator, documented in detail, including the reason, date, personnel involved, and participant status, and reported to the ethics committee when required.

To minimize visual cues during treatment, participants will be positioned so that the needling procedure is not in their direct line of sight. For acupoints on the forearm and anterior chest, an opaque drape or screen will be used where feasible, and participants will be instructed not to observe needle insertion or removal. For back acupoints, participants will be unable to directly observe the procedure. The same adhesive pads, treatment setting, participant position, verbal instructions, and session duration will be used in both groups. The sham needles will have a similar external appearance to real needles but will be blunt-tipped and non-penetrating. These procedures are intended to reduce visual and contextual differences between groups.

### Interventions

2.7

Participants in both groups will continue conventional medical therapy recommended by current guidelines for chronic coronary syndromes and INOCA, including anti-anginal agents for symptom relief and preventive treatment for cardiovascular risk-factor control (2). To minimize potential bias related to pharmacotherapy, all participants will be required to have a relatively stable medication regimen for at least 1 month before enrollment. Guideline-directed conventional medical therapy will be continued in both groups throughout the trial. Medication changes during the study will be avoided unless clinically necessary. Any change in drug type, dose, timing, or indication will be recorded in detail, and substantial medication changes will be considered in sensitivity or exploratory analyses where appropriate.

#### Acupuncture group

2.7.1

Participants in the acupuncture group will receive true acupuncture in addition to conventional drug therapy. The prespecified acupoints are Dabao (SP21), Neiguan (PC6), Danzhong (CV17), Xinshu (BL15), and Geshu (BL17). The nomenclature and locations of these acupoints follow the national standard GB/T 12346–2021 (25). Their surface locations and detailed information are shown in Figure 2 and Table 2.

**Figure 2 F2:**
[figure not shown]
Locations of the acupoints.

**Table 2 T2:** Locations of the acupoints used in this study.

Acupoint	Location
Dabao (SP21)	In the lateral thoracic region, in the 6th intercostal space, on the midaxillary line.
Neiguan (PC6)	In the anterior forearm region, 2 cun proximal to the palmar wrist crease, between the tendons of palmaris longus and flexor carpi radialis.
Danzhong (CV17)	In the anterior thoracic region, on the anterior median line, at the level of the 4th intercostal space.
Xinshu (BL15)	In the upper back region, at the level of the lower border of the spinous process of the 5th thoracic vertebra, 1.5 cun lateral to the posterior median line.
Geshu (BL17)	In the upper back region, at the level of the lower border of the spinous process of the 7th thoracic vertebra, 1.5 cun lateral to the posterior median line.

During each session, participants will sit comfortably with the area below the elbows and the chest, hypochondriac region, and back exposed. After routine skin disinfection, adhesive pads will be placed over the selected acupoints. Disposable sterile stainless-steel filiform needles (0.30 mm × 40 mm; Huatuo, Suzhou, China) will then be inserted through the pads to an appropriate depth sufficient to elicit deqi. After insertion, manual needle manipulation will be performed to elicit deqi, typically described as soreness, numbness, distension, or heaviness. No specific tonification or sedation technique will be prespecified. During the 20 min retention period, no additional routine manipulation will be performed unless required to maintain deqi according to the standardized procedure. Treatment will be administered three times weekly, every other day, with 20 min of needle retention per session for 4 consecutive weeks. Further details of the intervention, including the number of needle insertions, unilateral or bilateral point use, depth of insertion, response sought, and needle stimulation, are provided in Supplementary Table S2.

#### Sham acupuncture group

2.7.2

Participants in the sham acupuncture group will receive sham acupuncture in addition to conventional drug therapy, using the same acupoints and treatment schedule as the acupuncture group. After routine disinfection and placement of adhesive pads, a blunt-tipped sham needle (0.30 mm × 25 mm; Huatuo, Suzhou, China) will be applied so that it passes through the pad and touches the skin surface without penetrating the skin or subcutaneous tissue, and deqi will not be sought. The sham procedure will be matched with true acupuncture in terms of acupoint location, participant position, treatment environment, treatment frequency, session duration, and overall treatment course. Contact pressure will be kept light and as consistent as possible across sessions. The needle-withdrawal procedure will be identical to that in the acupuncture group.

All procedures will be performed by licensed traditional Chinese medicine practitioners certified by the National Health Commission of the People's Republic of China, each with at least 2 years of clinical experience in acupuncture.

### Outcome measures

2.8

#### Primary outcome

2.8.1

The primary outcome is the overall clinical response rate at week 4, defined as the proportion of participants who achieve an increase of at least 5 points in the Seattle Angina Questionnaire summary score (SAQ-SS) from baseline. The Seattle Angina Questionnaire (SAQ) is a disease-specific 19-item instrument comprising five domains—physical limitation, angina stability, angina frequency, treatment satisfaction, and quality of life—with each domain scored from 0 to 100; higher scores indicate better angina-related health status (26). The SAQ-SS is calculated as the mean of the physical limitation, angina frequency, and quality-of-life domain scores (19). Consistent with previous studies, an increase of 20 points or more will be considered a large improvement, an increase of 5–19 points a clinically meaningful improvement, and an increase of less than 5 points, no change, or deterioration as no response (27, 28). The responder rate will be calculated as the number of participants with an SAQ-SS increase of at least 5 points divided by the total number of participants.

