## Discussion

3

CMVD remains a therapeutic challenge even after diagnostic recognition, and the gap between pathophysiological classification and meaningful symptom improvement is still substantial (38, 39). This exploratory sham-controlled trial therefore focuses on a clinically relevant question: whether acupuncture can provide incremental benefit beyond stable conventional therapy in patients with persistent symptoms. This question is important because symptom burden, functional limitation, and health status remain central concerns in CMVD care, and structured patient-reported outcome measures are increasingly emphasised in mechanism-based management pathways (21, 30).

A further strength of the protocol is its multidimensional outcome framework. In CMVD, symptom relief alone may not fully reflect treatment response. Combining SAQ-based health-status assessment with endothelial and inflammation-related biomarkers may improve interpretation of early-phase trial findings and help generate hypotheses regarding potential biological pathways (17, 31).

The choice of sham acupuncture as the control is methodologically important in this trial. Because key outcomes such as SAQ-based health status, angina frequency, and CGI-I are vulnerable to expectation and contextual effects, sham acupuncture may better control for non-specific effects related to practitioner attention, treatment ritual, and patient-provider interaction than usual care alone. In this study, the sham group receives the same acupoints and treatment schedule as the acupuncture group, but with non-penetrating blunt-tipped needles, in order to strengthen participant blinding and improve internal validity. However, sham acupuncture may not be completely physiologically inert, which should be considered when interpreting between-group differences.

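### Response needs a 5-point SAQ-SS rise, but eligibility sets no upper limit on baseline SAQ-SS, so a participant who starts above 95 can be randomised and cannot respond in either arm

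*Protocol article*

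**What the plan says.** Section 2.8.1 defines response at week 4 as "an increase of at least 5 points in the Seattle Angina Questionnaire summary score (SAQ-SS) from baseline". It describes the SAQ domains "with each domain scored from 0 to 100; higher scores indicate better angina-related health status", and adds: "The SAQ-SS is calculated as the mean of the physical limitation, angina frequency, and quality-of-life domain scores". It classes "an increase of less than 5 points, no change, or deterioration as no response", and the responder rate is the number of responders "divided by the total number of participants".

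Eligibility rests on two diagnoses together. The Western diagnosis (section 2.2.1.1) begins with "Typical clinical symptoms are present" and adds at least one objective sign of ischaemia and non-obstructive angiography. The TCM diagnosis (section 2.2.1.2) requires chest pain or tightness, two or more secondary symptoms, and matching tongue and pulse signs. The inclusion list (section 2.2.2) adds age, a relatively stable regimen over the preceding month, and consent. Neither that list nor the exclusion list (section 2.2.3) mentions a SAQ score.

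The Discussion puts the trial's question as whether acupuncture gives "incremental benefit beyond stable conventional therapy in patients with persistent symptoms". Under section 2.6 each envelope is opened "only after eligibility has been confirmed and baseline assessment has been completed", and randomisation is simple and not stratified by baseline SAQ score.

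**The concern.** A responder endpoint that requires a fixed rise on a bounded scale needs room above the baseline value. Here the room is guaranteed neither by the definition of response nor by the entry criteria. A patient whose angina is well controlled by the stable regimen that the protocol requires can meet both diagnoses, start above 95, and be counted as a failure whatever the treatment does.

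Such a patient also fits poorly with the population of persistent symptoms that the Discussion describes but that the criteria do not enforce.

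What is at stake is mainly planning information. Section 2.10 says the sample size was chosen to give preliminary estimates, the week 4 responder rate among them, for the design and size of later confirmatory trials. Participants who cannot respond pull that rate and the between-group difference down.

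**Working it through.** The plan gives no figure for the baseline SAQ-SS distribution, the response rates or power, so there is none to reproduce on this point. The ceiling follows from the plan's definitions. The size of its effect rests on assumptions, marked below.

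**1. Ceiling.** From section 2.8.1, the maximum SAQ-SS is (100 + 100 + 100)/3 = 100, so the largest possible rise is 100 − baseline.

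| Baseline SAQ-SS | Largest possible rise | Response possible? |
|---|---|---|
| 90 | 10 | yes |
| 95 | 5 | yes, just |
| 96 | 4 | no |
| 98 | 2 | no |
| 100 | 0 | no |

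A score above 95 means that the deficits in the three domains add up to less than 3 × 5 = 15 points. Domain scores of 100, 90 and 100, for example, give 290/3 = 96.7.

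**2. Do the criteria prevent it?** Sections 2.2.1.1 and 2.2.1.2 require symptoms to exist. Neither says how severe, how frequent or how recent they must be. Sections 2.2.2 and 2.2.3 add nothing on this. A score above 95 is therefore unlikely for a typical entrant but is not excluded.

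**3. How many? (assumption)** Take baseline SAQ-SS as normal with mean 60–80 and SD 15–20, truncated to 0–100, with Φ the standard normal distribution function:

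share above 95 = [Φ((100 − m)/s) − Φ((95 − m)/s)] / [Φ((100 − m)/s) − Φ((0 − m)/s)]

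- m = 60, s = 15: 0.6%, or 60 × 0.006 ≈ 0.4 participants of 60.
- m = 80, s = 20: 8.1%, or 60 × 0.081 ≈ 5 participants of 60.

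Without truncation the second case gives 22.7%, but 15.9 points of that lie above 100, where no score can be. The untruncated figure would apply only if that mass sat exactly at 100.

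**4. Effect on the endpoint.** If a share c in each arm cannot respond and the rates among the others are p1 and p0, the observed rates are (1 − c)p1 and (1 − c)p0. Their difference is (1 − c)(p1 − p0). As an illustration, assume p1 = 60%, p0 = 30%, 30 per group and two-sided 5%:

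| c | Of 60 | Rates | Difference (points) | Odds ratio | Power | n per group for 80% power |
|---|---|---|---|---|---|---|
| 0 | 0 | 60.0% vs 30.0% | 30.0 | 3.50 | 65% | 42 |
| 5% | 3 | 57.0% vs 28.5% | 28.5 | 3.33 | 61% | 47 |
| 10% | 6 | 54.0% vs 27.0% | 27.0 | 3.17 | 57% | 51 |

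The 10% row lies just above the truncated range in step 3 and is best read as an upper bound, unless scores pile up at 100. The trial has no power target. The last two columns matter only as a guide to how a later trial planned on these rates would be affected.

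**The case against.** The best counter-argument is that the entry criteria already make the case rare. Both diagnoses must be met, and together they ask for chest pain or tightness, at least two further symptoms, tongue and pulse signs, and objective ischaemia. Sections 1 and 2.8.3 describe the population as symptomatic. This stands as an argument that the share is small. It does not close the gap, because no severity, frequency or recency is set.

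Second, this is an exploratory pilot without a formal sample size calculation. SAQ-SS is also analysed as a continuous outcome, and baseline SAQ is recorded for everyone, so the pilot will itself show how many started above 95. That is fair, and it is the main reason to call the point minor. It does not remove the effect on the primary outcome, and leaving out such participants after randomisation would depart from the intention-to-treat analysis of section 2.11.

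Three stronger readings are tempting, and the document supports none of them:

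- A reader might infer that more than a fifth of participants could be at the ceiling. That comes from an untruncated normal curve, most of whose tail lies above the top of the scale, and nothing in the document supports a mean near 80.
- A reader might infer that participants between 90 and 95 are also lost. They are not: a baseline of 90 allows a rise of 10, twice the threshold. A ceiling of 90 would exclude people who can respond.
- A reader might infer that the result is biased toward one arm. In expectation the ceiling acts equally in both. Simple unstratified randomisation could split a few such participants unevenly, but only by chance.

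**Conclusion.** The point holds as a minor improvement. It is certain, from the plan's own definitions, that a baseline SAQ-SS above 95 rules out response and that no criterion keeps such a participant out. How many there will be is unknown. About 0.6% to 8%, or roughly 0 to 5 of 60, follows from the assumed truncated normals, and the share would be larger if scores cluster at 100.

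The consequence is dilution by the factor (1 − c). At 5%, an assumed 30-point difference becomes 28.5. The estimate remains valid for the population as enrolled, but it understates the responder rate among patients who are able to respond. No statement in the protocol is wrong on this point; the gap lies between the endpoint definition and the entry criteria.

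**What to change.** Add one eligibility criterion: baseline SAQ-SS no higher than 95, checked at the baseline assessment before the envelope is opened. Count those above it as screen failures and replace them, so that 60 are still randomised. The value 95 is the arithmetic limit and removes only people who cannot meet the endpoint.

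The enrolment wording has to change with it. Section 2.1 places the baseline assessment within 24 hours after enrolment, and Table 1 puts eligibility screening on day −1 and the SAQ on day 0. Both should state that eligibility is final only once the baseline SAQ has been scored. The order already set in section 2.6 can stay.

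The cost is a few more screen failures, slightly slower recruitment and a marginally narrower population. No new visit, instrument or analysis is needed.
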